## Abstract

**Background:**

Diabetes education together with patient empowerment has shown to be key to effective self-management behavior. When delivered through information and communication technologies (ICT), this solution has shown to lead to better health outcomes. However, the potential of ICT and their integration into the healthcare environment have not yet been fully exploited. ICT should be in particular used to facilitate communication and information exchange between patient and healthcare providers. In addition, systems should include components facilitating behavior change using empowerment approaches such as goal-setting.

**Discussion:**

The interplay between multiple sources, including EHR, patients’ own registered information and physicians’ recommendations on one platform can have important practice implications. It might not only improve self-management activities in diabetes patients but it will also facilitate physician’s work, and ultimately the physician patient relationship.

**Trial registration:**

The trial has been registered with Deutsches Register Klinischer Studien (German register of clinical trials) under DRKS00007699 on January 30, 2015.

## Background

Diabetes, and in particular diabetes type 2, is one of the fastest growing chronic diseases in nowadays society [1]. Tight blood glucose control, dietary requirements and regular medication intake are only few of the things that a diabetes patient needs to manage in order to prevent long-term complications [2]. Given that continuity of care has to be guaranteed, this does not only pose many challenges for the patient but also for the treating physician who will need to support the patient’s management strategies.

Research has shown that diabetes education is central to effective self-management behavior, which in the long term can influence clinical [3] and psychological outcomes [4]. Lately, approaches have moved from purely educational interventions to those that empower patients based on the assumption that they are managers of their own health [5,6]. The term patient empowerment refers to a process that enables and facilitates behavior change. The key to empowerment does not necessarily lie in an increased compliance to what the doctor says or prescribes but rather in the opportunity to increase patients’ autonomy, and to improve their decision-making capacities [7].

Given the pervasiveness of Information and Communications Technologies (ICT) and their potential, eHealth and mHealth applications have become particularly popular for interventional approaches that aim at empowering patients. Studies in diabetes patients using web-based approaches have indeed shown to effect empowerment levels [8]. With regard to clinical outcomes, web-based interventions were able to reduce blood glucose levels [9] and hospitalization rates [10]. Even though effects found were in general rather small [11], web-based approaches, compared to traditional approaches, yield promising results [12]. Regarding the effectiveness of mobile applications, there is only few solid evidence on diabetes treatment so far, given that the field of mHealth is still very young [13,14]. However there are some recent encouraging findings that underscore the potential of mobile use in combination with web-based approaches for diabetes education purposes [11,15].

Most web-based interventions, so far, have not been comprehensively embedded into the healthcare environment surrounding the individual patient. Therefore, more systematical approaches are needed. Personal health records (PHR) that are linked to electronic health records (EHR) have shown to be a promising solution. PHRs allow patients to manage and share their health information using secure pathways with others who are authorized to see them [16]. Particularly in chronic disease management PHRs are of considerable value given that diabetes patients require constant care and regular follow-ups. In addition, time and resource constraints in physicians’ everyday practice make PHRs even more useful [17].

Studies that included PHRs and focused on diabetes were able to show that the use of PHRs linked to EHRs would increase for instance the adjustment of diabetes related medication [18] or improve blood glucose levels [19].

Goal-setting is one of the key components facilitating behavior change with the empowerment approach [7]. Goal-setting helps patients to act more independently by providing feedback on their self-management behavior thereby also sustaining motivation and increasing problem-solving skills and self-reflection. Goal-setting does not necessarily have to refer to purely clinical outcomes but also to psychological outcomes such as self-efficacy, which in the long run might influence the continuity or increase of an action set as a goal [20]. Even though goal-setting in collaboration with the treating physician is favorable, only few studies so far were able to show an active involvement of the treating physician. Studies showed that most physicians were reluctant to actively get involved, due to time and resource constraints. The usage of computer-based programs has shown to be helpful to, at least partly, circumvent these issues [20]. However, in spite of physicians’ reluctance, most of the interventions, including non-diabetes related studies, that used for example PHRs were mostly physician-oriented and did not take sufficiently the patients’ needs into account. For example, patients were only able to access their information via their physicians or treating hospitals. Besides, the general lack of additional information on diabetes treatment or any form of patient support proved those systems to be less attractive to patients [21].

In general, ICT should be used to facilitate communication and information exchange between patient and healthcare providers, which is fundamental to the motivation of the patient. ICT should not rely solely on information provision and data insertion but also contribute to an interactive exchange between the patient and his/her healthcare providers [22-24].

### Objective

The current study aims at increasing empowerment and self-management behaviors in a sample of diabetes patients type 1 and type 2 in Germany and Turkey by:Providing a web-based application, available also for mobile devices, that allows patients to regularly upload their personal health records in form of blood glucose measures or journal entries regarding physical activity, nutrition, etc.giving patients the opportunity to systematically define goals and track their improvements over the course of the interventionintegrating physicians’ treatment goals and recommendations into the systemsystematically integrating the web-based application with electronic and personal health records

## Methods/Design

### The web-based application

The development of the application (EMPOWER system – Figure 1) encompasses four main objectives. The first one is to foster self-management with adaptive and secure patient pathways. The pathways are iterative and adaptable to the patients’ skills (access, competence and motivation), requirements and needs, which will be assessed by the system according to different maturity levels. Maturity levels – novice, advanced, and expert – refer here to the stage reached by the patient in learning to self-manage his/her diabetes management tasks.

**Figure 1 Fig1:**
[figure not shown]
**EMPOWER cycle.**

A second objective is to support behavioral changes by integrating actions in patient’s daily life through personalized action plans. These actions plans will be based on recommendations from the treating physicians, personalized long-term goals, diabetes-relevant information material, and patients’ preferences. In addition, actions can be related to reminders in order to bring them timely into the patient’s mind. The third objective is to facilitate self-control by collecting patterns of daily living. Therefore, services for observations of daily living (ODLs) that allow patients to upload vital, physical (e.g. blood glucose levels) and mental parameters and physical and lifestyle activities are included in the system. The last objective is to include an open-source PHR system, which can be integrated into existing PHR or EHR systems. In turn, the EMPOWER system aims at integrating services from these other health applications. Semantic interoperability is supported on the basis of established standards (i.e. ISO/CEN13606 information models).

The EMPOWER system goes beyond already available diabetes self-management applications as it also involves the patients’ treating physician. During a routine consultation at the beginning of the intervention phase the collaborating physicians will specify treatment goals and recommendations regarding self-management goals together with the patient. This goal setting serves as the basis for the use of the EMPOWER system. Based on the patient’s consent the treating physician will be able to access the patient’s EMPOWER records and follow the patient’s self-management activities. Consequently, physicians will be able to detect possible causes for changes in the patient’s condition, such as fluctuating blood glucose levels. In addition, the physician will be able to discuss the patient’s goal pursuit process and to give advice on diabetes self-management.

From a user experience perspective the EMPOWER system is divided into two main blocks. The first block targeting the treating physician is called *recommender engine*. The second block is the *self-management portal*, dedicated to the patients. The physician can monitor the patient’s health status through the recommender engine, which receives input from the patient’s Observations of Daily Living (ODLs). As a result, the physician can give the patient recommendations. A patient can check his/her physician’s recommendations, set his/her personal goals and plan his/her weekly activities in the self-management portal (Figure 2).

**Figure 2 Fig2:**
[figure not shown]
**Self-management portal: Physician’s recommendations to the patient.**

The patient can create journal entries during the week in order to get an overview of his/her progress, and use the review at the end of the week to evaluate the journal entries and to plan the activities of the forthcoming week. The patient decides on his/her own whether or not to grant access to his/her data to the physician by using the consent editor.

As a constant support, the patient can also access a section called patient information material, which offers disease related information and can be of help in planning goals and activities. The information material has been written in English for EMPOWER and then translated into German and Turkish. The material is based on existing and acknowledged information sources and educational material for diabetes patients. Since patients suffering from diabetes have different levels of knowledge, the material is designed to address different information needs: from basic information to more detailed, and from generic information to practical advice. For this purpose the Patient Information Material has been structured along three levels of content: Knowledge, Management, and Advice.

### Pretest of the EMPOWER Platform

The pilot application was pretested during a first validation phase in Germany and Turkey. Fifteen diabetes patients, thereof seven from Germany and eight from Turkey, first received a training on how to use the EMPOWER system and then used it for two months. Feedback on usability and usefulness was gathered quantitatively via standardized questionnaires as well as qualitatively through a roundtable discussion. The results of the first validation phase were then used to further develop the system and eliminate existing difficulties. Besides, the seven patients from Germany also participated in the pretest of the questionnaire on self-management that will be used as a baseline and post-intervention measure to assess the effectiveness of the EMPOWER system.

### Study design

The study is planned as a pre-post-design by administering questionnaires before and after the intervention. The aim is to recruit up to 70 participants at both study sites and then randomly assign them to either the intervention or control group.

After being recruited participants will be asked to give their informed consent. They will then be administered an online questionnaire containing various measures on self-management and socio-demographics to assess their baseline values before using the EMPOWER system. In order to create familiarity with the tool all participants will take part in an introductory training. There, patients will be taught how to download, use, and integrate the application into their daily life.

Participants are supposed to use the system regularly for a period of three months. They will be contacted via telephone on a weekly basis to gather feedback on usability, discuss potential problems concerning the tool and reduce the loss to follow-up. After the intervention has ended patients are again asked to fill in an online questionnaire containing the same measures as the pre-questionnaire plus questions on usability and usefulness of the tool.

### Ethical approval

The project was approved by the Bavarian State Office for Data Protection, Germany and by the Scientific Researches Evaluation Commission of the Ministry of Health of the Turkish Republic.

### Recruitment

It is planned to recruit overall 140 patients. The calculation of 140 participants (70 patients at each study site) is based on a previous study by Schulz and colleagues [25] in the field of web-based interventions. Eligible participants are between 18 and 65 years of age and suffer from diabetes type 1 or 2. Moreover, they need to have access to internet, own a computer or smart phone and be able to use the EMPOWER application.

In Germany, participants will be recruited via the practice network GOIN in Ingolstadt, Bavaria. The network comprises about 500 medical specialists and general practitioners who care for about 200.000 patients. The administrative staff from the practice network will be in charge of the recruitment of the patients and physicians for the main study. This will be done through personal contact with network members and advertising in practices and the network’s magazine.

Turkish participants will be recruited at the Hitit University Endocrinology Clinic of Turkey in Ankara. The Turkish Ministry of Health collaborates with two endocrinologists, two diabetes nurses, and one dietician at the University hospital who will recruit the participants among their patients, and also hired participants for the pretest.

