#### Self-management activities

The impact of patient empowerment on self-management activities through the use of the EMPOWER system will be assessed by measuring the patients’ pre- and post-intervention health status, diabetes self-care, health literacy, doctor-patient communication, and empowerment. To assess an overall effect of the application on the health status as perceived by the patient, a self-reported, one item measure will be used. Patients will be asked to rate their health independently from their diabetes to avoid negatively biased answers due to the chronic condition. Diabetes self-care will also be measured subjectively, using the SDSCA as developed by Toobert and Glasgow [32] and revised by Toobert and colleagues [33]. The scale focuses on the patients’ self-care across various dimensions such as diet, exercise, blood sugar testing, foot care, and smoking. The questions refer to the last seven days of a participant’s routine diabetes self-care and therefore represent a comprehensive insight into the patient’s self-management that will be completed by the objective data stemming from the user tracking.

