### Data analysis

Data will be analyzed using the statistics software package SPSS, version 21, from IBM. To detect possible changes and their predictors’ descriptive statistics and regression analyses will be applied. In order to compare pre- and post-results as well as control and intervention group dependent and independent t-tests will be calculated.

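### The named between-group t-test cannot account for diabetes type, a factor known at entry, so some precision may be lost; this is an efficiency point, not a validity error

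*Protocol article*

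**What the plan says.** Under Objective, the platform is tested "in a sample of diabetes patients type 1 and type 2 in Germany and Turkey". Under Recruitment, the entry criterion is "Eligible participants are between 18 and 65 years of age and suffer from diabetes type 1 or 2". No quota or expected mix of the two types is given.

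Under Study design, the plan is to "randomly assign them to either the intervention or control group". Ratio, method and stratification are not described there.

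Under Self-management activities, the self-care scale covers "self-care across various dimensions such as diet, exercise, blood sugar testing, foot care, and smoking", with reference to the preceding seven days.

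Under Data analysis, the comparison is assigned as follows: "In order to compare pre- and post-results as well as control and intervention group dependent and independent t-tests will be calculated". The same section plans descriptive statistics and regression to detect changes and what predicts them, without naming a covariate. It does not say whether the independent t-test uses post-intervention scores or change from baseline.

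**The concern.** Diabetes type is checked at eligibility, so it is known for every patient before allocation. It is plausible, though not stated in the article, that usual self-care differs between the types, above all blood sugar testing. If so, an analysis that ignores type leaves the between-type variance in the error term. Any chance difference in type mix between the arms then shifts the estimate obtained in this one trial.

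The two sites recruit through different channels, a German network of practitioners and specialists and a Turkish hospital endocrinology clinic, so the mix may also differ by site.

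Precision matters here. The Background describes effects of web-based programmes as generally small. The Limitations expect dropouts and warn that change within three months may be hard to detect.

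**Working it through.** **The plan's own figure.** "It is planned to recruit overall 140 patients", at 70 per site: 2 x 70 = 140, which agrees. The article gives no effect size, SD, alpha or power, so the total cannot be rebuilt from design inputs. The percentage reductions in steps 1 and 3 do not depend on sample size. The other steps assume 1:1 allocation, 70 per arm.

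**Assumptions (none from the documents).** Type 1 share p = 0.2 to 0.5. Gap between types g = 0.5 or 1.0 within-type SD. Within-type variance set to 1.

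**Step 1: comparison of post scores.** Ignoring type, the variance is V = 1 + p(1-p)g². Accounting for type leaves 1. The standard error falls by 1 - 1/√V.

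| p | p(1-p) | V at g = 0.5 | SE cut | V at g = 1 | SE cut | 140 x V at g = 1 |
|---|---|---|---|---|---|---|
| 0.2 | 0.16 | 1.040 | 1.9% | 1.16 | 7.2% | 162 |
| 0.3 | 0.21 | 1.0525 | 2.5% | 1.21 | 9.1% | 169 |
| 0.5 | 0.25 | 1.0625 | 3.0% | 1.25 | 10.6% | 175 |

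The last column is the number of patients an unadjusted analysis would need to match 140 analysed with type. At p = 0.1 the cuts are smaller: 1 - 1/√1.0225 = 1.1% and 1 - 1/√1.09 = 4.2%.

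**Step 2: the same in power.** Take an effect that gives the unadjusted t-test 80% power at two-sided 0.05 with 70 per arm (0.47 total SD). Over p = 0.2 to 0.5, adjusting for type raises power to 81.5-82.3% at g = 0.5 and to 85.5-87.9% at g = 1.

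**Step 3: what type adds once the baseline score is in the model.** Let v = p(1-p) with g = 1 at both time points, and let r be the within-type pre-post correlation, assumed 0.4 to 0.8. Residual variance with baseline only is (1+v) - (r+v)²/(1+v). With type added it is 1 - r². The ratio of the second to the first simplifies to (1+r)(1+v)/(1+r+2v), and the SE cut is 1 minus its square root.

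| p | r = 0.4 | r = 0.8 |
|---|---|---|
| 0.2 | 2.8% | 0.8% |
| 0.3 | 3.5% | 1.0% |
| 0.5 | 4.0% | 1.1% |

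Example: p = 0.5, r = 0.4 gives 1.4 x 1.25 / 1.9 = 0.921, square root 0.960, a cut of 4.0%.

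**Step 4: change scores.** If the gap is the same before and after, it drops out of post minus pre. Type then explains nothing, and the gain is near zero.

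**Step 5: chance imbalance.** With unstratified 70/70 allocation, the hypergeometric probability of a difference of at least 10 points in type 1 share is 0.138, 0.196 and 0.237 at p = 0.2, 0.3 and 0.5. At g = 1 a 10-point difference moves the estimate by 0.10 x 1 = 0.1 SD. The standard error is √(2/70) = 0.17 SD, so this is about 0.6 of one standard error.

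**Step 6: validity.** The unadjusted t-test was simulated with no treatment effect, 70 per arm, p = 0.2 and 0.5, g = 0.5 and 1, 20,000 runs each. Type I error was 0.0485 to 0.0532, and the absolute bias was below 0.002 SD. Imbalance in type is random noise already reflected in the standard error.

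**The case against.** **The article is condensed, and stratification may sit in the full protocol.** This stands. A reader might infer that patients are randomised without regard to type, but the article says only that assignment is random. Silence on the method is not evidence that type is ignored. The objection has less force for the analysis, because the article does name the test. If the full protocol does stratify by type, the case for a type term in the model grows, since a t-test would not use the balance achieved.

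**Regression is planned too.** True, and those models could carry type. However, Data analysis gives them the task of finding predictors of change, names no covariates, and gives the group comparison to t-tests.

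**Chance imbalance is not bias.** Correct. A reader might infer that an uneven type mix creates a false treatment effect. It can shift a single estimate, but step 6 shows no bias and no inflation of type I error.

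**Nothing in the article says that type drives self-care.** Also correct. The self-care dimensions are listed without reference to type. The size of the gap is an assumption, most plausible for blood sugar testing and less argued for empowerment, health literacy or communication.

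**Baseline adjustment does most of the work.** Largely so. By step 3, type adds about 1-4% at a 1 SD gap. By step 4, a change-score test already removes a stable difference. The article does not say which score is tested.

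**Conclusion.** The point holds as one of efficiency, of small to moderate size. The named group comparison leaves out a factor that is known at entry and costs nothing to include.

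For post scores and 20-50% type 1, the avoidable standard error is 2-3% at a 0.5 SD gap between types and 7-11% at 1 SD. Beyond baseline adjustment it is about 1-4% at 1 SD, for within-type pre-post correlations of 0.4 to 0.8. It is near zero if change scores are tested and the difference between types is stable. All of this depends on type being prognostic and on assumed shares and gaps that the article does not give.

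The documents do not support saying that the t-test is invalid or biased, or that randomisation disregards type.

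**What to change.** Replace the between-group t-test with a prespecified regression (ANCOVA) of the post score on group, baseline score, site and diabetes type. Show the blood-sugar-testing dimension of the self-care scale descriptively by type as well as overall.

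The cost is one extra model term and one table. Type is already recorded at eligibility, so no further patients, visits or measurements are needed.

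Stratifying the randomisation by type is optional. It would be enough for the randomisation description to state whether type is a stratification factor.
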